### Outcomes

The feasibility of a full trial will be monitored throughout the study (eg, the randomization, recruitment, and retention of participants; data collection; and adherence). Additional data will be collected only on intervention participants. These include data on engagement with the PARITY intervention based on the number of hyperlinks clicked, time engaged in the content, and the number of doula sessions completed throughout the 12 weeks. A total of 10 to 15 intervention participants will be asked to complete a qualitative interview to discuss their experiences with the intervention and the acceptability of the technology component, doula component, and strength messaging component at 12 weeks post partum.

Clinical maternal outcomes (maternal blood pressure, gestational weight gain, delivery modality, and exploratory perinatal outcomes) will be measured at 20 weeks, 36 weeks, birth, and 6 weeks post partum and will be collected from the medical record. At baseline (20-28 weeks’ gestation), demographics, discrimination, and neighborhood variables will be assessed using self-report questionnaires administered via REDCap (Research Electronic Data Capture; version 14.3.11) [30,31]. At baseline and 6 to 12 weeks post partum, wellness-related behavior outcomes (nutritional intake, physical activity, and sleep quality) and empowered strengths (self-efficacy, social support, problem-solving, motivation, resilience, and self-regulation) will be measured using web-based self-report questionnaires in REDCap. In addition, health care adherence (the number of prenatal appointments) will be evaluated retrospectively using medical records.

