
### Data Analysis

Participants will be described using standard summary statistics and distribution plots of measured variables at each point in time. We will estimate the standardized magnitude of each baseline difference and the correlation between each baseline variable and each outcome of interest in the interim and primary end point of early participants to objectively determine baseline variables that will be needed to estimate the unbiased effect of PARITY on each outcome. A shared random component generalized linear mixed model (GLMM) will be used to simultaneously describe and compare the effects of PARITY on clinical outcomes, wellness-related behavioral outcomes, and empowered strength outcomes over the measurement periods [49]. A shared random component model will account for the correlation within participants on any 1 measure and the correlation between measures on the same participant at the same time point. The effect of time will be treated as a fixed effect. The time-by-group interaction will be tested; if the interaction *P* value is >.10, it will be dropped from the model. Baseline nutrition, physical activity, and sleep measures will be used as covariates to control for potential differences in the groups and to avoid detecting spurious time-by-treatment interactions due to the random assignment of participants to groups. Demographic or clinical characteristics exhibiting differences between groups at baseline will be investigated as potential covariates in the models. For significant effects, preplanned post hoc contrasts will be computed, and *P* values will be adjusted using the Holm method to maintain comparison-wise error at or <.05 [50]. Unless otherwise specified, the significance level for all tests will be.05.

Missing outcome data caused by loss of follow-up are possibly related to the participant’s unobserved outcome measures (nonignorable missingness). The GLMM provides unbiased estimates under missing completely at random and missing at random mechanisms. The data will be reanalyzed using a pattern-mixture model (PMM) to allow for different coefficient changes based on dropout patterns [51]. GLMM and PMM marginal treatment effects will be compared. If the marginal treatment effects differ by >10%, the missingness mechanism will be assumed not at random, and the PMM model marginal estimates will be used to draw conclusions.

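### For nutrition, physical activity and sleep, the analysis read literally uses baseline as both response and covariate; the covariate cannot give the interaction test the stated protection and may make its standard error modestly too small

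*Protocol article*

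**What the plan says.** The Outcomes section gives these three outcomes two measurement times: "At baseline and 6 to 12 weeks post partum, wellness-related behavior outcomes (nutritional intake, physical activity, and sleep quality". The Outcome Measures section repeats this for each instrument.

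The Data Analysis section fits one generalized linear mixed model for the "effects of PARITY on clinical outcomes, wellness-related behavioral outcomes, and empowered strength outcomes over the measurement periods". It adds that "The effect of time will be treated as a fixed effect" and that the time-by-group interaction will be tested, and dropped if its P value exceeds .10. Within-person correlation is handled by a random component: "A shared random component model will account for the correlation within participants on any 1 measure".

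The same section then has baseline nutrition, activity and sleep "used as covariates to control for potential differences in the groups and to avoid detecting spurious time-by-treatment interactions due to the random assignment" of participants. It does not exempt the three outcomes whose own baseline is named, and it mentions no covariate-by-time term.

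**The concern.** With two occasions, time and time-by-group terms can be fitted only if the baseline value is a response. If it is also a covariate, the same number stands on both sides of the model. Two consequences follow.

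- The stated purpose is not met. A covariate with one value per participant cancels out of within-person change, so it cannot remove the effect of a chance baseline difference on the time-by-group estimate.
- The model's residuals are distorted. Regressing a response partly on itself makes a participant's two residuals negatively correlated. A random component with non-negative variance cannot represent that.

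At stake are the interaction test and the effect sizes for three objective 3 outcomes. The article says the pilot is to supply effect sizes.

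**Working it through.** **The plan's own figures.** The article gives no figure for this test. Its detectable differences of 0.81 SD (25 per group) and 0.91 SD (20 per group) reproduce as 0.809 and 0.909 with a two-sample t test. They are stated for blood pressure and gestational weight and are not used below.

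**Inputs.** From the article: 30 per group, two occasions, two-sided .05, attrition up to 20%. Assumed: normal outcomes, equal variances (SD = 1), and rho of 0.3 to 0.7, because the article does not give rho.

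**Step 1: the estimate.** Write Y0 for baseline, Y1 for follow-up and b for the covariate slope. The term b·Y0 is the same at both times, so it drops out of Y1 − Y0. In complete data the time-by-group estimate is therefore the raw difference in mean change, with or without the covariate. Fitted models agreed to about 1e-15.

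**Step 2: chance imbalance.** Given a baseline difference d0, the expected follow-up difference under no effect is rho·d0. The change contrast therefore shifts by rho·d0 − d0 = −(1−rho)d0. Simulated slopes were −0.69, −0.50 and −0.30 at rho 0.3, 0.5 and 0.7. The standard error of d0 is sqrt(2/30) = 0.26 SD, so at rho 0.5 a one-standard-error imbalance shifts the estimate by 0.5 × 0.26 = 0.13 SD. When the follow-up value is the response and its own baseline the covariate, the slope on imbalance is −0.005 to 0.013.

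**Step 3: the standard error with a bounded random component.**

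- The covariate slope is 1 for the baseline response and rho for the follow-up response, so the pooled slope is (1+rho)/2.
- The residual variances are ((1−rho)/2)² at baseline and 1 − rho² + ((1−rho)/2)² at follow-up.
- The residual covariance is ((1−rho)/2) × (rho − (1+rho)/2) = −((1−rho)/2)². It is negative, so the random-intercept variance goes to 0. This happened in 98–100% of simulated fits.
- The model then takes the variance of change as the sum of the two residual variances, (1−rho)(3+rho)/2. The true value is 2(1−rho). The ratio is (3+rho)/4.
- Type I error = 2 × (1 − Phi(1.96 × sqrt((3+rho)/4))).

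| rho | SE ratio | Type I error, formula | Simulated, variance refitted | Simulated, variance set to 0 |
|---|---|---|---|---|
| 0.3 | 0.91 | 7.5% | 6.9% | 7.6% |
| 0.5 | 0.94 | 6.7% | 7.0% | 6.7% |
| 0.7 | 0.96 | 5.9% | 5.8% | 6.4% |

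The simulations use 30 per group. At rho 0.5 the refitted runs without the covariate gave 5.8%, so part of that 7.0% is simulation noise. A joint model of three outcomes at rho 0.5, closer to the simultaneous analysis planned, gave an SE ratio of 0.936 and 6.8% rejection.

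**Step 4: sensitivity to the model.** With an unrestricted covariance that allows negative correlation, the standard error was correct in complete data. With 20% dropout at rho 0.5 the SE ratio was 0.91, against 0.86 (8.4% rejection) for the bounded random component.

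**The case against.** The double use is inferred. No sentence says that these baselines are responses while they are covariates, and the time sentences are written for all outcomes together, including cesarean birth, which has no repeated values. A reader could take the 6–12-week value as the response and baseline as covariate only. This stands as a caution, but it does not rescue the text: on that reading the three outcomes have one response occasion, no time-by-group term, and nothing for the stated rationale to protect.

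A covariate-by-time term would remove both problems. The estimate then equals the baseline-adjusted comparison of follow-up values, and simulated rejection was about 5.0–5.6%. Such a term, or the covariance structure, may be in a full protocol or analysis plan that is not shown. This also stands, and it is why the point is conditional. The article nevertheless states what the covariates achieve, and the model it describes does not achieve it.

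The sentence has another purpose, controlling for group differences. That is legitimate for a group main effect and is not disputed here.

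A reader might infer that chance imbalance biases the treatment effect. It does not: the shift is conditional on the imbalance observed and averages to zero over randomization. At rho 0.5 the change contrast has a standard error of sqrt(4 × 0.5/30) = 0.26 SD, which already includes it. A reader might also infer a loss of power at 0.81 SD. The article states that difference only for blood pressure and gestational weight, and comparing change scores with baseline adjustment measures efficiency, not error.

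**Conclusion.** The point holds in limited form. For nutrition, activity and sleep, the model as literally described cannot deliver the protection claimed for the interaction test. That part needs only complete data and no covariate-by-time term.

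The standard-error part needs more: a random component with variance bounded at zero. Its size is then modest, at 4–9% too small, with type I error of about 6–7.6% for assumed rho of 0.3–0.7 and complete data. It would be wrong to conclude that the standard error is too small under any covariance structure.

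It would also be wrong to extend the standard-error part to the primary outcome. In a check with four occasions, as for blood pressure, a participant-level covariate left the interaction estimates and standard errors unchanged. The affected outcomes belong to objective 3 of a 60-person pilot, so severity is minor to moderate.

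**What to change.** In Data Analysis, use each baseline once for these three outcomes, in one of two ways:

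- Take the 6–12-week value as the response with that outcome's own baseline as covariate, fit no time-by-group term, and report the group coefficient as the effect.
- Keep baseline as a response, constrain the group means to be equal at baseline, and remove that baseline from the covariates for that outcome.

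Replace the claim about time-by-treatment interactions with a purpose that the chosen model can serve. If the full plan already has a covariate-by-time term, the article should say so.

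The cost is wording and model code, with no new data, visits or participants. Under the first option, a participant with follow-up but no baseline would need the constrained form. Randomization follows completion of the enrollment surveys, so this should be rare.

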**Methods:**

A 2-arm RCT and mixed methods evaluation will be conducted. Overall, 60 Black pregnant individuals will be randomized in a ratio of 1:1 to either the intervention or informational control group. Participants in the intervention group will receive access to the technology platform over a 12-week period that ends before birth. Intervention participants will be assigned a doula interventionist, who will meet with them 4 times during the intervention. All participants (intervention and control) will receive a referral for a birth doula at no cost, printed materials about having a healthy pregnancy, and community resources. Feasibility and acceptability will be assessed at the end of the program. Measures will be obtained at baseline (20-28 weeks), the 36th week of pregnancy, birth, and 6-12 weeks post partum. Summary statistics and distribution plots will be used to describe measured variables at each time point. A generalized linear mixed model with a shared random component will be used to analyze the effects of PARITY on clinical, wellness behavioral, and empowered strength outcomes, including baseline nutrition, physical activity, and sleep measures as covariates. For significant effects, post hoc contrasts will be adjusted using the Holm method to maintain comparison-wise error at or <.05. Missing data will be addressed using a pattern-mixture model.

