Maternal blood pressure (primary) at 20 weeks, 36 weeks, birth, and 6 weeks post partum will be measured retrospectively from the medical record at 12 weeks post partum. The data will be analyzed as a continuous variable using the participant’s blood pressure (systolic and diastolic) as well as categorically with the blood pressure classifications of hypertension (>140/90) and severe hypertension (>160/110).Gestational weight gain (secondary), or the amount of weight gained in pounds at 20 weeks, birth, and 6 weeks post partum, will be measured retrospectively from the medical record at 12 weeks post partum.Cesarean birth (secondary) will be assessed from the delivery modality (vaginal, cesarean, or assisted vaginal delivery), measured retrospectively from the medical record at 12 weeks post partum.Perinatal outcomes (exploratory) from birth will be measured retrospectively at 12 weeks post partum via the maternal medical record. The perinatal outcomes that will be measured include preterm delivery; gestational diabetes; birth weight; gestational age at delivery; anesthesia used during labor; labor length; delivery provider type (obstetric physician, family physician, resident physician, or certified nurse midwife); and intrapartum medical diagnoses according to theInternational Classification of Diseases, 10th Revision[34], including hypertensive disorders of pregnancy, intrapartum fever, and postpartum hemorrhage. In addition, the Appearance, Pulse, Grimace response, Activity, and Respiration score of the newborn at birth will be measured as a way to summarize the health of the baby [35].

The following outcome measures will be used to investigate changes to wellness behavioral outcomes and empowered strengths:

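### Covariates are to be picked from chance baseline differences and early outcome correlations, with no thresholds, while baseline blood pressure, weight and strengths scores are not fixed as covariates

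*Protocol article*

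**What the plan says.** The Data Analysis section of the protocol article gives three routes into the adjustment set.

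- **Screen on early data.** The team will estimate the standardised size of every baseline difference and "the correlation between each baseline variable and each outcome of interest in the interim and primary end point of early participants". The purpose is "to objectively determine baseline variables that will be needed to estimate the unbiased effect of PARITY on each outcome".
- **Screen on imbalance.** "Demographic or clinical characteristics exhibiting differences between groups at baseline will be investigated as potential covariates in the models".
- **Fixed covariates.** "Baseline nutrition, physical activity, and sleep measures will be used as covariates to control for potential differences in the groups". The Abstract names the same three and no others.

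Neither screen has a threshold or a closed list of candidates, and the number of early participants is not given.

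On the primary outcome, the Outcome Measures section says: "Maternal blood pressure (primary) at 20 weeks, 36 weeks, birth, and 6 weeks post partum will be measured retrospectively from the medical record". Enrolment is at 20 to 28 weeks (Study Population), so the 20-week reading serves as a pre-randomisation value. It is not named as a covariate. Nor is the 20-week weight value or the baseline score of any empowered-strengths scale.

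The main model is a shared random component GLMM over the measurement periods. Its time-by-group interaction is dropped when its P value exceeds .10.

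**The concern.** In a 1:1 randomised trial, a baseline difference between arms arises by chance. The unadjusted comparison is already unbiased over repeated randomisations, so no screen is needed for that purpose. Adjustment is worthwhile because it gains precision and corrects for chance imbalance in a variable that predicts the outcome. Both benefits are best obtained by naming prognostic variables in advance, and an outcome's own earlier value is usually the leading candidate.

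The plan works the other way round. It fixes three lifestyle measures for every outcome and leaves baseline blood pressure to enter only if it passes a screen with no stated cut-off, or as the first response in the repeated-measures model. The text does not say which. Without thresholds, two analysts could follow the same paragraph and reach different adjustment sets. The trial is meant to supply effect sizes for a larger trial, so an estimate that depends on such choices is a poor input.

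**Working it through.** **1. The protocol's own figures.** Inputs from the sample-size section: two-sided Welch t test, alpha .05, 80% power, 25 per group, or 20 after 20% attrition. With equal arms and equal variances, the noncentral t with 2n − 2 degrees of freedom gives 0.809 SD at n = 25 and 0.909 SD at n = 20. The stated 0.81 and 0.91 reproduce. They are unadjusted figures.

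**2. With baseline blood pressure as a fixed covariate.** Detectable difference = (noncentral t value with 2n − 3 degrees of freedom) × √(1 − ρ²), where ρ is the correlation between baseline and follow-up blood pressure. The protocol gives no ρ, so it is assumed.

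| ρ (assumed) | √(1 − ρ²) | 25 per arm | 20 per arm |
|---|---|---|---|
| none (unadjusted) | 1 | 0.81 | 0.91 |
| 0.3 | 0.954 | 0.77 | 0.87 |
| 0.5 | 0.866 | 0.70 | 0.79 |
| 0.7 | 0.714 | 0.58 | 0.65 |

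**3. Error control given a chance imbalance.** At 25 per arm, a baseline difference above 0.5 SD means |z| > 0.5/√(2/25) = 1.77, which has probability 7.7%. Given that event and no treatment effect, the unadjusted test rejects with probability P(|ρz + √(1 − ρ²)e| > 1.96), where e is an independent standard normal variable. This is about 9%, 16% and 28% for ρ = 0.3, 0.5 and 0.7. Simulation with the t test gives 9%, 16% and 27%.

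**4. Overall type I error.** Simulation at 25 per arm with no effect and ten independent baseline variables, one of them blood pressure (all assumed), for ρ = 0.3 / 0.5 / 0.7:
- adjust for blood pressure only if its baseline test has P < .05: 5.0% / 4.7% / 3.7%;
- adjust for any variable with a standardised difference above 0.5: 4.4% / 4.4% / 3.4%;
- the same, or an absolute correlation above 0.3 in the first half of participants: 4.6% / 4.7% / 5.2%;
- report the most favourable of four models (unadjusted, fixed, and the last two rules): about 7% / 9% / 10%.

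**5. Precision.** In the same simulation at ρ = 0.7, the standard error of the effect is 0.285 unadjusted, 0.269 with the imbalance rule, 0.213 with imbalance or early correlation, and 0.207 with fixed adjustment. Relative to fixed adjustment, the imbalance rule alone costs 0.269/0.207 = 1.30, and the combined rule 0.213/0.207 = 1.03.

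**6. How often the imbalance screen fires.** With 7 to 10 independent variables tested at .05, at least one differs by chance with probability 1 − 0.95⁷ = 30% to 1 − 0.95¹⁰ = 40%. With a cut-off of 0.25 SD at 30 per arm, each variable crosses with probability 33%, and at least one of ten does so with probability 1 − 0.67¹⁰ = 98%. The number of variables and both cut-offs are assumptions. The spread shows how much rests on the missing threshold.

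**7. If the 20-week reading is only a response.** Suppose the interaction is dropped and the true effect is δ at 36 weeks, birth and 6 weeks post partum. An equally weighted group effect over four times is (0 + δ + δ + δ)/4 = 0.75δ. It is diluted by one quarter and is not baseline-adjusted.

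**The case against.** The strongest defence is that baseline blood pressure is not shut out. It is listed as a measurement of the primary outcome, so the GLMM can carry it as a response, and it is a candidate in the correlation screen. If that screen works well, little precision is lost: about 3% in standard error at ρ = 0.7 under the assumed cut-offs. Characteristics are to be investigated as covariates, not entered automatically; the trial is a pilot; and an article may leave a covariate list to the analysis plan.

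Much of this stands, and it limits the size of the point. It does not remove it. The article is not silent: it states a selection rule and a reason for it, and the reason is wrong. The response route helps only while the interaction is retained; step 7 shows what follows when it is dropped.

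Several stronger readings are tempting but unsupported:

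- *The P values are invalid.* A mechanically applied imbalance rule is nominal or conservative overall. The 7% to 10% arises only if someone picks the most favourable model. The protocol does not plan that, although its missing thresholds leave room for it.
- *The early look is unplanned or unblinded.* It is written into the plan. A correlation between a baseline variable and an outcome needs no allocation data, and the imbalance screen needs no outcome data.
- *No outcome has its own baseline named.* Nutrition, physical activity and sleep are repeated outcomes, and their baselines are fixed covariates.
- *The fall from 0.81 to 0.70 SD is what the plan loses.* That comparison is with the unadjusted t test, not with the GLMM plus screens.

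**Conclusion.** The point holds in a limited form. The protocol chooses covariates from chance imbalance and early outcome correlations, without thresholds and on a mistaken rationale. It does not fix the baselines of blood pressure, weight or the strengths scales.

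The consequences are lost precision, raised conditional error when baseline blood pressure happens to be imbalanced (about 9% to 27% if left unadjusted, for ρ from 0.3 to 0.7 and an imbalance above 0.5 SD), and analyst discretion. Overall type I error is not shown to be inflated. Against the unadjusted test, the detectable difference at 25 per arm could fall from 0.81 SD to between 0.77 and 0.58 SD. The gain over the planned analysis is smaller and cannot be stated without the thresholds.

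The dilution by one quarter is conditional: the 20-week value must be a response, the interaction must be dropped, and the effect must be equal at the three later times. All figures that use ρ, the number of variables or a cut-off rest on assumed values.

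**What to change.** Make two changes to the Data Analysis section before outcome data are analysed.

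1. Pre-specify each repeated outcome's own pre-randomisation value as a covariate: 20-week blood pressure for blood pressure, 20-week weight for the weight outcomes, and the baseline score for each questionnaire. Alternatively, specify a longitudinal model with baseline means constrained equal between arms and the effect estimated at post-baseline times only.
2. Delete the imbalance screen and the early-participant screen, with the statement that they are needed for an unbiased effect. If they are kept, label them as sensitivity analyses with stated candidates and thresholds.

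The pre-specified nutrition, activity and sleep covariates may stay. The cost is wording only, because these baseline values are already scheduled for collection. That cannot be said of every possible covariate: the article mentions pregnancy history but does not show that prior cesarean is recorded, so the fix does not rely on it.

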### Sample Size Calculation for Future Full-Scale RCT

A sample size of 25 participants per group is sufficient to measure the proportional outcomes of recruitment efficiency and attrition for each group separately with an SE ≤0.10, assuming no attrition and worst-case variability (0.25) in each group. Past research suggests that attrition of up to 20% is acceptable and limits bias [26,27]. If there is up to 20% attrition in each group, the SE for each proportional outcome will be ≤0.12.

On the basis of Welch 2-sample 2-tailed *t* test, a minimum sample size of 25 participants per group provides 80% power to measure a difference in mean blood pressure and gestational weight change between the intervention and control groups of 0.81 multiplied by the SD, using a significance level of .05 [25]. If there is up to 20% attrition in each group, a difference of 0.91 multiplied by the SD is detectable with 80% power using a significance level of.05 [25]. We will recruit at least 5 additional participants per group, planning for screen failures or participant withdrawals.

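### The 10% rule for switching from the mixed model to the pattern-mixture model cannot show that missingness is not at random, and it often lets chance choose the reported estimate

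*Protocol article*

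**What the plan says.** Data Analysis states that the GLMM is unbiased when data are missing completely at random or at random, and that loss to follow-up may be nonignorable. It continues: "The data will be reanalyzed using a pattern-mixture model (PMM) to allow for different coefficient changes based on dropout patterns". The two marginal treatment effects are then compared: "If the marginal treatment effects differ by >10%, the missingness mechanism will be assumed not at random", and in that case "the PMM model marginal estimates will be used to draw conclusions". Trigger and consequence are therefore both fixed in the text. The trigger refers to no standard error or confidence interval.

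The same section sets a model-reduction step for the time-by-group interaction: if its "P* value is >.10, it will be dropped from the model".

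The number of occasions differs by outcome. Outcome Measures lists "Maternal blood pressure (primary) at 20 weeks, 36 weeks, birth, and 6 weeks post partum", taken from the medical record. Outcomes gives the questionnaires two occasions: "At baseline and 6 to 12 weeks post partum, wellness-related behavior outcomes (nutritional intake, physical activity, and sleep quality) and empowered strengths". Health care adherence comes from the medical record.

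**The concern.** There are three difficulties.

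- **The inference.** Missing at random and not at random differ only in how the unobserved values relate to dropout. A difference in observed trajectories between dropouts and completers is compatible with missing at random, so a gap between two fitted models does not identify the mechanism.
- **The threshold.** It is a fixed percentage of the estimated effect. The smaller the estimate, the smaller the absolute gap that triggers the switch, whatever the sampling error.
- **The two-occasion questionnaires.** A participant lost before the post partum survey has a baseline value only. The PMM is meant to give dropout patterns their own change, but nothing in the data estimates that change.

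The pilot is meant to supply effect sizes for a larger trial. Under this rule, chance would often decide which of two estimates is carried forward.

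**Working it through.** **Inputs from the protocol.** 30 per arm, 1:1 (Study Design). A minimum of 25 per arm, attrition up to 20%, detectable differences of 0.81 SD and 0.91 SD, 80% power, two-sided .05 (Sample Size Calculation for Future Full-Scale RCT). The 10% switch and the P>.10 step (Data Analysis).

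**Assumed, not in the protocol.** Correlation 0.5 between visits, linear time, monotone dropout, true effects of 0 to 0.81 SD.

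**1. The plan's own figures.** Two-sample t test, noncentrality d × √(n/2). The plan states "a minimum sample size of 25 participants per group provides 80% power" for 0.81 SD. With n = 25 the noncentrality is 0.81 × √12.5 = 2.86, power is 80.1% and the detectable difference is 0.809 SD. With n = 20 it is 0.91 × √10 = 2.88, power 80.1%, detectable difference 0.909 SD. Both stated figures reproduce.

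**2. Threshold against noise.** With 20% attrition, 30 × 0.8 = 24 per arm are observed. The SE of a mean difference is √(2/24) = 0.289 SD.

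- Effect 0.81 SD: threshold 0.081 SD; 0.081/0.289 = 0.28 SE.
- Effect 0.3 SD: threshold 0.03 SD; 0.03/0.289 = 0.10 SE.

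The two estimates share data, so their difference varies less than either one does. The firing rate therefore needs simulation.

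**3. Firing rate under the stated procedure.** 30 per arm, four visits, 20% dropout with numbers varying by arm. Both models were fitted by generalized least squares with the random-intercept covariance treated as known, which favours the rule. The PMM had separate dropout coefficients averaged over pattern proportions. The interaction was dropped if P>.10. There were 900 replicates under completely random dropout and 500 under a not-at-random mechanism (MNAR) in which intervention dropouts end 0.5 SD worse.

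| True effect (SD) | Random, dropouts seen at 2-3 visits | MNAR, same visits | Random, some baseline only | MNAR, some baseline only |
|---|---|---|---|---|
| 0 | 53% | 54% | 63% | 63% |
| 0.3 | 42% | 53% | 59% | 61% |
| 0.5 | 45% | 48% | 56% | 57% |
| 0.81 | 37% | 44% | 51% | 57% |

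The ratio of MNAR to random firing runs from 63/63 = 1.00 to 53/42 = 1.26, so firing says little about the mechanism.

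A second simulation took the effect at the last visit and weighted patterns by their proportions within each arm (600 replicates, dropouts seen at 2-3 visits, P>.10 step included). At the same four effects it gave 45%, 45%, 49% and 51% with 20% dropout, and 39%, 41%, 46% and 45% with 10% dropout.

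**4. Dependence on the interaction step.** With the interaction always kept, 20% random dropout gives 83%, 71%, 60% and 41% in the first simulation (87%, 82%, 72% and 56% if some dropouts have baseline only), and 89%, 81%, 71% and 55% in the second. For the group main effect with dropout numbers forced equal by arm, it is only 32%, 13%, 3% and 0%.

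**5. Two-occasion questionnaires.** With separate intercept, time, group and time-by-group terms for completers and dropouts there are 8 mean parameters. Observed cells: completers 2 groups × 2 times = 4, dropouts 2 groups × baseline = 2, total 6. The rank is 6 of 8, and the dropouts' time and time-by-group terms have no data. At 20% attrition this concerns about 30 × 0.2 = 6 people per arm.

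Two usual restrictions show the consequence. The marginal effect is 0.8 × (completers' effect) + 0.2 × (dropouts' effect). Take the GLMM estimate as roughly the completers' effect, E.

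- Borrowing the completers' change makes the dropouts' effect E, so the marginal effect is E. This is a missing-at-random answer, and the gap is about zero by construction.
- A shift of δ makes the marginal effect E − 0.2δ. The gap exceeds 10% exactly when δ > 0.5E: 0.405 SD for E = 0.81, 0.15 SD for E = 0.3. The chosen δ decides the result.

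**The case against.** The strongest reply is that the harm is modest. Under completely random dropout the switching estimator was essentially unbiased relative to the GLMM and type I error was 5.4-6.5%. With the P>.10 step, the significance verdict changed in about 1% of trials at zero effect and 5-11% at 0.3-0.81 SD. The loss of precision at 20% dropout was up to about 13%, and of power up to about 9 points. This stands. A reader might infer that the rule biases the trial or badly inflates false positives; the calculations do not support that.

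Blood pressure comes from records released at enrollment, so someone who skips the post partum survey may still supply all four readings. The 20% is an upper planning bound. This also stands: with nearly complete records the rule fires less often for the primary outcome.

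An article may leave pattern definitions and identifying restrictions to a fuller plan. That is fair, so the unnamed restriction is not itself the defect. But neither restriction examined above makes the 10% comparison informative.

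A reader might also infer that the rule fails for every objective 3 outcome. It does not: health care adherence is drawn from records. Nor does the abstract's "Missing data will be addressed using a pattern-mixture model" contradict the main text; it condenses it. Finally, the article says the mechanism will be assumed, not proven, and this is a pilot. Even so, conclusions follow from that assumption.

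**Conclusion.** The switch is wrong as written. It draws an inference that observed data cannot support, using a threshold blind to sampling error. With 30 per arm, four visits, correlation 0.5, 10-20% random dropout and the P>.10 step, it fires in roughly 40-65% of trials (individual scenarios 37-63%).

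It is tempting to say that the rule fires mostly on noise, or nearly always when the effect is near zero. That matches the rates with the interaction always kept (about 45-90% in most scenarios, down to 23% at 10% dropout, 0.81 SD and equal dropout numbers). The documented procedure drops the interaction when P>.10, and there the rate at zero effect is 45-63% with 20% dropout.

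The similarity to the MNAR rates holds for the 0.5 SD departure. With a 1 SD departure, the interaction always kept and equal dropout numbers, firing rose from 34% to 71% at a 0.81 SD effect. Even there it fired in a third of trials whose dropout was random.

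For the two-occasion questionnaires the 10% comparison is uninformative, and this does not depend on the simulation assumptions.

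**What to change.** Delete the 10% switch from Data Analysis. State that conclusions rest on the likelihood-based GLMM under missing at random. Report the PMM as a sensitivity analysis and say whether the conclusion holds. For questionnaires with only baseline and one post partum measurement, use a delta-adjusted analysis over a range that the team fixes in advance; the protocol offers no basis for a particular range. Set both before outcome data are compared by arm.

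The cost is a wording change and a few sensitivity runs. No new data are needed.
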